### Randomization

Eligible patients will be randomly assigned 1:1 to immediate stenting or deferred stenting after primary angioplasty and informed consent (Fig. 1). Random allocation sequence has been generated by using a computer-based system before recruitment started, and results are encrypted and uploaded to a network accessible to all research centers routinely in stacks of sealed electronic envelopes that can be uncovered only with passwords when patients are enrolled. The block size is 4. When a patient is eligible in one center, the investigators of that center will download and open the electronic envelope with passwords obtained from the system and get the result of random allocation and will report the information of enrollment in an online research database which will inform all of the other investigators.

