### Clinical procedures

PCI procedures are performed in accordance with each clinical center’s standard routines. There are no restrictions on the balloons, guide wires, thrombus aspiration, or intra-aortic balloon pump usage. The choice of transradial or transfemoral approach will be determined by the operator. We recommend that the participating centers apply the minimalist immediate mechanical intervention (MIMI) technique with small balloon dilatation and thrombus aspiration for the pretreatment. New-generation drug-eluting stents are applied in all participating centers, and the exact type and size of the stents are possibly different. For immediate stenting, stents are implanted immediately after blood flow is regained by interventional pretreatment. Deferred stenting is scheduled 4–15 days after primary angioplasty and in the same hospitalization period. Immediate stenting will be applied if TIMI grade 3 flow cannot be retrieved and these cases will not be enrolled in analysis. CABG is considered as an alternative and will be scheduled within 6 h after PCI procedure failure. For the deferred stenting group, stent implantation will be canceled at the operator’s discretion if the patient is unsuitable for deferred stenting or stent implantation is unnecessary during the second PCI. These patients will be excluded from the per-protocol set but will still be in the intention-to-treat set.

All patients will be transferred to the coronary care unit after the primary angiographic procedure. Intravenous glycoprotein IIb/IIIa inhibitor will be maintained for 18–36 h after PPCI. A loading dose of aspirin and P2Y12 inhibitors will be given before the procedure. An intravenous bolus of unfractionated heparin (100 U/kg) will be administrated right before the procedure to achieve therapeutic activated clotting time. Dual-anti-platelet therapy will be maintained during the deferred period and for at least 1 year after PCI. The peri-procedural treatment is in accordance with the Chinese guidelines for the management of AMI [21].

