### Outcomes

#### Primary endpoints

Since the study is focused on the optimal interventional strategy for patients with LM-AMI in order to reduce the mortality and incidence of adverse events, the primary endpoint is a composite of all-cause mortality or recurrent MI at 30 days after PPCI.

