### Statistical analyses

Numerical data are summarized with means and standard deviations or medians with interquartile ranges depending on the distribution. Categorical data were described as proportions and percentages. Comparisons of numerical variables are conducted with the Student *t* test. Categorical variables and outcomes were compared by using the chi-squared test or Fisher exact test. All tests were two-tailed with a significant level of 0.05. Logistic regression is applied to adjust the significant variables in baseline data between the two groups and assess the outcomes presented with odds ratios and 95% confidence intervals. All data are analyzed by independent statisticians blinded to the random allocation using Stata version 14.0 and SAS version 9.4 (or higher versions of these programs).

The statistical analyses of primary and secondary outcomes will be conducted in both the intention-to-treat set and the per-protocol set. According to the intention-to-treat principle, all of these eligible patients who actually did not receive deferred stenting will still be included in the intention-to-treat analysis. In the per-protocol set, patients who undergo randomization but withdraw consent to participate or not treated according to the allocated procedure after randomization will be excluded from per-protocol statistical analyses.

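### The per-protocol rule can remove deferred-arm patients because of what happens to them while they wait for the stent, and the protocol does not say that intention-to-treat decides

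*Protocol article*

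**What the plan says.** All of this is in the Methods of the protocol article.

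- **Randomization:** "Eligible patients will be randomly assigned 1:1 to immediate stenting or deferred stenting after primary angioplasty and informed consent".
- **Clinical procedures, immediate arm:** "stents are implanted immediately after blood flow is regained by interventional pretreatment".
- **Clinical procedures, deferred arm:** "Deferred stenting is scheduled 4–15 days after primary angioplasty and in the same hospitalization period". The Abstract gives 4–10 days for the same interval.
- **Primary endpoints:** "the primary endpoint is a composite of all-cause mortality or recurrent MI at 30 days after PPCI". The Abstract counts the 30 days from randomisation. On either count the deferred arm's wait falls inside the window.
- **Clinical procedures, cancelled stents:** in the deferred group, "stent implantation will be canceled at the operator’s discretion if the patient is unsuitable for deferred stenting", or if a stent proves unnecessary at the second procedure. "These patients will be excluded from the per-protocol set but will still be in the intention-to-treat set".
- **Statistical analyses, per-protocol set:** patients who withdraw consent or are "not treated according to the allocated procedure after randomization will be excluded from per-protocol statistical analyses".
- **Statistical analyses, use of the sets:** "The statistical analyses of primary and secondary outcomes will be conducted in both the intention-to-treat set and the per-protocol set". Tests are two-tailed at 0.05. The section applies the intention-to-treat principle to eligible patients who did not receive deferred stenting, and it ranks neither set above the other.

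**The concern.** Being treated as allocated means different things in the two arms. In the immediate arm it is settled within the index procedure. In the deferred arm it is settled days later, after a period in which the patient can die, have another infarction or be judged unsuitable. Entry to the per-protocol set therefore depends on what happens after randomisation, and almost only in one arm. A deferred-arm patient who dies on day 2 has not received the allocated stent. An immediate-arm patient who dies on day 2 has received it, and stays in the set with the event.

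This is the familiar immortal-time problem. If early events leave the deferred arm's numerator and denominator, the per-protocol comparison leans towards deferral, which is the direction of the trial's hypothesis. The same rule also removes deferred-arm patients whose lesion needs no stent at the second look. That finding is produced by the strategy under test, and these patients may well be at low risk, so removing them can bias the comparison the other way.

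At stake is the reading of a significant per-protocol result, or of a disagreement between the two sets, when the document does not say which set carries the conclusion.

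**Working it through.** **Figures in the plan.** The protocol gives no figure for the effect of the per-protocol rule, so there is none to reproduce. The Sample size section supplies three inputs: an event rate p = 22.9%, a planned relative decrease of 35%, and 240 patients per arm (216 after 10% loss). The 22.9% is labelled annual; I use it as the 30-day risk because the plan sizes the primary endpoint on it. Whether 240 per arm follows from those inputs is a separate question, and nothing below depends on it.

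**Assumed input.** f is the share of deferred-arm primary events that are dropped with their patients because they precede the scheduled procedure. The documents do not give it. I show 10% to 40%. For orientation only: if events were spread evenly over 30 days, a wait of 4 days would contain 4/30 = 13% of them and a wait of 15 days 15/30 = 50%. Events clustered early would raise f. Patients who re-infarct but are still stented on schedule would lower it.

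**Step 1: early events dropped, no true effect.** The immediate arm stays at p. The deferred per-protocol risk is

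p(1 − f) / (1 − pf).

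With 240 per arm the expected deferred-arm events are 240 × 0.229 = 54.96. For f = 25%, 13.74 are removed, leaving 41.22 events in 226.26 patients: 18.2%, and 18.2/22.9 = 0.80. The false-positive rate is that of a two-sided pooled z test at 0.05, by normal approximation.

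| f | Patients removed | Deferred per-protocol risk | Risk ratio | False positives |
|---|---|---|---|---|
| 0% | 0 | 22.9% | 1.00 | 5% |
| 10% | 5.5 | 21.1% | 0.92 | 8% |
| 25% | 13.7 | 18.2% | 0.80 | 24% |
| 40% | 22.0 | 15.1% | 0.66 | 56% |

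The risk ratio equals 0.65, the planned effect, when f = (1 − 0.65)/(1 − 0.65 × 0.229) = 0.41.

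**Step 2: sensitivity of step 1.** With 216 per arm the false-positive rates at f = 10%, 25% and 40% are 7%, 22% and 52%. With a true risk of 15% instead of 22.9%, 240 per arm and f = 25%, the risk ratio is 0.78 and the rate about 18%.

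**Step 3: add the stent-unnecessary exclusions.** As an illustration, assume that 24 of the 240 deferred-arm patients need no stent and have no event.

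- f = 10%: (54.96 − 5.50)/(240 − 5.50 − 24) = 49.46/210.50 = 23.5%; risk ratio 23.5/22.9 = 1.03.
- f = 25%: (54.96 − 13.74)/(240 − 13.74 − 24) = 41.22/202.26 = 20.4%; risk ratio 0.89, rejection about 10%.

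The second kind of exclusion can cancel or reverse the first.

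**Step 4: intention-to-treat.** All patients stay where they were randomised, so with no true effect the risk ratio is 1.00 and the rejection rate 5%.

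**The case against.** The strongest case against the point has five parts.

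1. **Intention-to-treat protects the main inference.** This stands. The protocol says explicitly that patients whose deferred stent is cancelled remain in that set. The bias is confined to the per-protocol result.

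2. **Equal standing is not stated.** A reader might infer that the two sets are co-primary and that a per-protocol result could carry the trial. The text says only that both analyses are done. A hierarchy is often left to the analysis plan, which is not shown, so nobody can say from this article that one is absent altogether. What remains is that the article fixes a per-protocol rule that depends on outcome, applies it to the primary endpoint at 0.05, and gives no order of precedence.

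3. **Death before the procedure is not named as an exclusion.** This also stands. A patient assigned to deferral, left unstented, who dies on day 2 could be said to have been managed as allocated. The rule's wording permits the opposite reading, though, and makes no exception. The exclusion of unsuitable patients is explicit, although on one reading that judgement is made only at the second procedure.

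4. **Bias towards deferral is not certain.** A reader might infer that the rule favours deferral by construction. Step 3 of the working shows why that does not follow: excluding patients who need no stent can offset or reverse the bias. Nor are losses strictly confined to one arm, since withdrawal and non-adherence can occur in both. Only the losses caused by waiting are specific to deferral.

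5. **The size rests on an assumed f.** This is true; the 56% needs f = 40%, and at f = 10% the inflation is modest.

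A reader might also suspect that the Clinical procedures sentence keeping patients without TIMI 3 flow out of the analysis removes randomised patients. The documents do not support that: TIMI 3 flow after pretreatment is an inclusion criterion in Table 1, and only eligible patients are randomised, after angioplasty.

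**Conclusion.** The concern holds for the per-protocol comparison and should be fixed. As worded, membership of that set is conditioned on post-randomisation outcome, almost entirely in the deferred arm. The component due to early events pulls towards deferral: with no true effect, risk ratios of about 0.92 to 0.66 and false-positive rates of about 8% to 56%. That rests on an assumed 10% to 40% of deferred-arm events being dropped, on 22.9% as the 30-day risk, on 240 per arm, and on pre-procedure death being read as not treated as allocated. The component due to unnecessary stents may pull the other way. The net size and direction cannot be known from the documents.

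The intention-to-treat analysis is sound on this point. That is why this is a should-fix matter and not a threat to the trial's main result, provided that the main result is declared to be the intention-to-treat one.

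**What to change.** 1. State in Statistical analyses that the deciding analysis of the primary endpoint is intention-to-treat: every randomised patient, in the allocated arm, whatever procedure was received. Label the per-protocol analysis supportive.
2. Define per-protocol adherence by strategy. A deferred-arm patient should not be excluded because of death, MI or clinically triggered revascularisation before the scheduled procedure, or because no stent was needed at the second look. Say how patients judged unsuitable are classified. Keep exclusion for departures from the assigned strategy without a clinical trigger. Amend the matching sentence in Clinical procedures so that the two sections agree.
3. Reconcile the 4–10 days in the Abstract with the 4–15 days in Clinical procedures. The window decides who counts as treated as allocated, so the per-protocol set is not fixed until the two agree.

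The cost is wording in the protocol and the analysis plan, best settled before any comparison by arm is seen. No new data and no extra patients are needed, although the classification does require that the date and reason for any unscheduled or cancelled procedure be available.

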### Study management

An independent CRA will monitor the study process and verify protocol compliance every 6 months. The CRA has access to all documents in the database, including original medical history, images, and CRFs. Data correctness will be assessed and serious adverse events will be reported to the ethics committee of the particular center and Zhongshan Hospital. The ethics committee of Zhongshan Hospital has the authority to terminate the trial according to local laws or institutional regulations. The investigators should keep the participating centers, ethics committee, and the journal informed of any major protocol modifications.

### Ethical considerations

This study is conducted in accordance with the ethical principles of the Declaration of Helsinki (2013). The protocol of this study has been read and approved by the ethics committee of participating hospitals. Printed informed consent and detailed information about the study will be offered to patients before randomization. The safety and feasibility of deferred stent implantation have been confirmed by several trials in patients with AMI [14, 15, 18]. All information and data of this trial are encrypted and stored in an online database accessible only to main researchers and administrators.

Patients primarily enrolled have rights to withdraw at any time point and the reasons will be documented. If patients in the deferred stenting group decided to withdraw between primary angiography and secondary PCI, stent implantation or CABG is still available for them while follow-up will be cancelled. In addition, PCI or CABG is ready for any patients presenting with recurrent ischemia and MI after stent implantation in the hospital.

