**Methods:**

The Optimal Strategy of Primary Percutaneous Coronary Intervention for Acute Myocardial Infarction due to Unprotected Left Main Coronary Artery Occlusion (OPTIMAL) study (ClinicalTrials.gov Identifier: NCT03282773) is an open-label, randomized, multicenter clinical trial in which 480 patients presenting with AMI caused by left main coronary artery occlusion recruited from 30 hospitals in mainland China will be randomly assigned 1:1 to immediate stenting or deferred stenting (scheduled 4–10 days after primary angioplasty) groups. The primary endpoint is a composite of all-cause mortality or recurrent myocardial infarction at 30 days after randomization. The secondary outcomes include all-cause mortality, cardiac death, recurrent myocardial infarction, and unplanned target vessel revascularization at 30 days, 6 months, and 12 months.

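### Cancelling follow-up for deferred-arm patients who withdraw before the second PCI can lose 30-day outcomes more often in that arm; the rule should be limited to refusal of further data collection and applied to both arms

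*Protocol article*

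**What the plan says.** All statements are in the Protocol article.

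- **Ethical considerations, general right:** "Patients primarily enrolled have rights to withdraw at any time point and the reasons will be documented". This covers both arms and says nothing about follow-up afterwards.
- **Ethical considerations, specific rule:** "If patients in the deferred stenting group decided to withdraw between primary angiography and secondary PCI", then "stent implantation or CABG is still available for them while follow-up will be cancelled". The immediate arm has no matching sentence.
- **Primary endpoints:** "the primary endpoint is a composite of all-cause mortality or recurrent MI at 30 days after PPCI".
- **Statistical analyses:** "all of these eligible patients who actually did not receive deferred stenting will still be included in the intention-to-treat analysis". The per-protocol set excludes "patients who undergo randomization but withdraw consent to participate" and, as a separate reason, patients not treated as allocated. No exclusion from the intention-to-treat set is given for withdrawal.
- **Clinical procedures:** patients whose deferred stenting the operator cancels leave the per-protocol set but stay in the intention-to-treat set.
- **Follow-up:** the 12-month follow-up is stated for all patients, with reminders by mail and phone. Table 2 gives history as the source for every endpoint.
- **Timing of the second PCI:** "Deferred stenting is scheduled 4–15 days after primary angioplasty and in the same hospitalization period" in Clinical procedures, but "deferred stenting (scheduled 4–10 days after primary angioplasty) groups" in the abstract. The two windows must be reconciled; this point holds under either.

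**The concern.** The cancellation is a written instruction, so an analysis plan that is not shown cannot repair it: outcomes that sites are told not to collect are not there to analyse. The sentence does not say whether withdrawing means refusing the second procedure, refusing further contact, or both. A site could therefore stop follow-up for a patient who only declines the scheduled stenting and would gladly answer a phone call at day 30.

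The opportunity is unequal between arms. Immediate-arm patients have had their allocated procedure at the index session. Deferred-arm patients wait for days, in an open-label trial, with a second procedure pending. If those who leave in that period differ in prognosis from those who stay, the comparison of 30-day death or MI is no longer protected by randomisation, although withdrawal is not a stated reason for leaving the intention-to-treat set. The 10% loss allowance in the sample size adds patients; it does not correct loss that depends on arm.

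**Working it through.** **Timing.** The second PCI falls at days 4–10 or days 4–15. Both windows close before day 30, so a withdrawal in the scheduled waiting period precedes the primary assessment.

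**Inputs from the Protocol article (Sample size).** Event rate 22.9%, planned relative reduction 35%, 240 patients per arm. The planned deferred rate is 22.9% × 0.65 = 14.9%, a difference of 8.0 points. The article calls 22.9% an annual rate although the endpoint is at 30 days; the relative risks below do not depend on it.

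**Inputs that are assumptions.** The article gives no withdrawal rate and no prognosis of withdrawers, so there is no figure of its own to reproduce here. Let w be the fraction of the deferred arm whose outcome is lost, and k their event risk divided by that of the patients who stay.

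**Step 1: what is left unknown.** If a fraction w has no outcome, the deferred-arm rate is undetermined over a range of width w: 2, 5 or 10 points for w = 2%, 5% or 10% (about 5, 12 or 24 of 240). About 20 patients (20/240 = 8.3%) would span the planned 8.0 points.

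**Step 2: apparent effect when there is none.** Let the true rate be p in both arms, with s the risk among stayers. Then p = (1 − w)s + w·k·s, so s = p/(1 − w + wk). If only retained patients are analysed and the immediate arm is complete, the apparent relative risk is s/p = 1/(1 − w + wk).

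| w | k = 0.5 | k = 1 | k = 2 | k = 3 |
|---|---|---|---|---|
| 2% | 1/0.99 = 1.01 | 1.00 | 1/1.02 = 0.98 | 1/1.04 = 0.96 |
| 5% | 1/0.975 = 1.03 | 1.00 | 1/1.05 = 0.95 | 1/1.10 = 0.91 |
| 10% | 1/0.95 = 1.05 | 1.00 | 1/1.10 = 0.91 | 1/1.20 = 0.83 |

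The corner w = 10%, k = 3 is extreme. With p = 22.9% the stayers' rate is 22.9%/1.20 = 19.1%, so withdrawers would have a risk of 3 × 19.1% = 57%, none of it observed.

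**Step 3: loss in both arms.** If the immediate arm also loses a fraction v with the same k, the apparent relative risk is (1 − v + vk)/(1 − w + wk). It equals 1 when v = w. With w = 10%, v = 5% and k = 2 it is 1.05/1.10 = 0.95. What matters is the difference in loss between arms, not the loss in the deferred arm alone.

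**The case against.** The strongest reply is that the sentence sits in an ethics paragraph, directly after the right to withdraw, so its natural subject is a patient leaving the study. Its evident purpose is to assure deferred-arm patients that treatment remains open to them. Missing outcomes after full withdrawal of consent limit any trial. This largely stands, and it rules out several stronger readings that a reader might infer:

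- *That the plan treats every departure from deferred stenting as the end of follow-up.* It does not. Patients whose stenting the operator cancels stay in the intention-to-treat set, and nothing stops their follow-up. The article also lists consent withdrawal separately from not receiving the allocated procedure.
- *That the plan contradicts its own intention-to-treat commitment.* The sentence keeping patients without deferred stenting in that analysis can be read as meaning the operator-cancelled group, whose outcomes are still collected.
- *That outcomes are lost in one arm only.* Immediate-arm patients may also withdraw, and no passage says they are then followed. Only the written rule and the additional waiting period are one-sided.
- *That the loss favours deferral.* Clinical unsuitability falls under operator cancellation, not withdrawal. A patient must also be alive to withdraw, so the earliest deaths all count among the stayers, which lowers k. Deferral takes place in hospital, so events before withdrawal should be on record. Nothing in the article fixes k above or below 1.

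Rules for missing outcomes and a best/worst-case analysis are ordinary analysis-plan content, so their absence here is no fault.

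What the reply does not answer is that the rule leaves withdrawal undefined, does not confine the cancellation to patients who refuse data collection, and is written for one arm.

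**Conclusion.** The point holds in a limited form. The clause allows 30-day death and MI outcomes to be lost by rule, in a period that exists only in the deferred arm and ends before the primary assessment, without requiring that the patient has refused further data collection. Outcomes may therefore be lost more often in that arm.

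Neither the size nor the direction of a resulting bias can be derived from the article. Under the assumed w and k, the effect runs from none (k = 1) through small (0.98 and 0.95 in the moderate cases) to 0.83 in an extreme case, and reverses if withdrawers are at lower risk. These figures assume that only retained patients are analysed and that the immediate arm is complete. Patients whose stenting is cancelled by the operator are not affected.

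This should be fixed, because uncollected outcomes may be unrecoverable and the repair is cheap. It does not show that the primary comparison is invalid.

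**What to change.** Replace the cancellation clause in Ethical considerations with a rule that applies to both arms:

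- Declining or changing the allocated procedure does not end follow-up.
- Death and MI are collected at 30 days, 6 months and 12 months for every randomised patient unless the patient refuses further data collection.
- For a patient who refuses, events up to the refusal are used, with vital status afterwards where consent allows.
- The numbers declining the procedure and the numbers refusing data collection are reported by arm.

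The cost is protocol and consent-form wording plus a few extra phone or record checks. Phone contact and history-based endpoints are already planned. The availability of treatment after withdrawal is untouched, and the sample size does not change. A patient's refusal of all data collection is still respected, so some outcomes may remain missing.
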